### Secondary trial outcomes

Secondary outcomes (Fig. 2) are:Days of hospital length of stay (LOS). This is defined as the continuous time spent in any type of inpatient hospital service (acute care, sub-acute rehabilitation, and time at another hospital) from the day of admission to the day of discharge to a community dwellingICU LOS in days;Unplanned ICU admission at any time point during the acute stay;Pneumonia, defined as the presence of new CXR infiltrates along with at least two of the following criteria: temperature >38 °C, dyspnoea, cough and purulent sputum, altered respiratory auscultation, and WCC >14,000/ml or leukopenia <3000/ml [65] on any day within the first 14 post-operative hospital days;Time in hours from end of operation to time able to achieve ambulation greater than 1 min;Time in days from end of operation to post-operative day able to achieve ambulation greater than10 min;Time in days to discharge from physiotherapy service (Table 4) [62];Time in days to readiness for discharge from hospital as defined by standardised scoring criteria [66];Hospital costs for the UAS admission episode of care. This will be supplied by the participating centres’ or health departments’ costing data for each participant’s admission episode.Patient-reported complications at 6 to 8 weeks following day of surgery using a standardised semi-structured interview; andHRQoL using the SF-36 and functional capacity using SAQ [58, 67] at 6 to 8 weeks following day of surgery.

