### Post-operative variables

Post-operative data will be collected daily for 14 days or until discharge from hospital, whichever occurs first: time in days from the pre-operative physiotherapy session to the operation; PPC risk stratification (low or high) using a defined risk calculation tool [5]; location (ICU, surgical ward, other) and duration in days at each location; days of analgesia and type (epidural, constant opioid infusion, patient controlled analgesia (PCA), patient controlled epidural analgesia (PCEA), oral, local pain infusion, or other); unplanned ICU/HDU admission and length of total ICU/HDU stay; length in days of total hospital stay; hours of mechanical ventilation; fluid delivery in the first 24 h (ml/kg/h); days and type of vasopressor use; hours and type of NIV use; days and types of oxygen therapy use; days, type, and indication for use for antibiotics; days and types of all drains and lines; day and diagnosis of a prolonged post-operative ileus using a standardised criteria [71] of 2 or more of the following factors in a 24-h period including nausea/vomiting, inability to tolerate normal diet, absence of flatus, abdominal distension, radiologic confirmation, and physician diagnosis of ileus.

Early ambulation parameters will be collected, including: time in hours from end of surgery until time to ambulation >1 min; post-operative day walked longer than 10 min; maximum rating of perceived exertion during ambulation at each session; maximum ambulation stage attained at each session (Table 2); number of assisted ambulation occasions; reasons for a patient being unable to participate in an ambulation session.

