### Sample size

Sample size was calculated using inference for proportions comparing two independent samples with a 0.05 two-sided significance level and will have 80 % power to detect a 10 % absolute difference in PPC between Pre-Op (estimated at 10 %) and an education booklet (estimated at 20 %) when the sample size is 398. This is further increased by 11 % to account for attrition, resulting in a final sample size of 441.

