### Statistical methods

The prognostic strength and size of imbalances to potential confounding baseline variables between groups will be assessed. Adjustment covariates will be selected by backward stepwise regression from covariates that may have the potential for clinically significant alterations in effect sizes. These include: history of a respiratory comorbidity, smoking history, self-reported physical activity levels, age, BMI, length in time of operation, operation category (upper gastrointestinal, colorectal, urological, other), ICU admission immediately following the procedure, incision type and location [72], intraoperative ventilation strategies [4, 73], fluid delivery [74], blood transfusions [75], mode of post-operative analgesia [76], and use of prophylactic antibiotics [50].

All outcomes are to be analysed using intention-to-treat. The absolute and relative rates of PPC in the trial groups will be estimated using multivariate robust random effects Poisson generalised linear regression to allow assessment of binary outcomes with or without adjustment for potential confounding variables (incidence rates and rate ratios, 95 % confidence intervals, *P*-values). Treatment centre will be treated as a fixed variable in the multi-level models. In addition, the effect of time from the end of surgery/anaesthesia to commencement of symptoms of PPC will be compared using Cox proportional hazards regression with and without covariate adjustment (hazards ratio, 95 % confidence intervals, *P*-values). Graphic representation of this analysis will be performed using the Kaplan-Meier method.

Binomial secondary outcomes, including pneumonia, unplanned ICU admission, and patient reported complications, will be analysed using mixed effects Poisson regression. Secondary outcomes with irregular distributions, including length of time periods (ICU and total post-operative LOS, time to ambulation for 1 and 10 min, and time to discharge from assisted ambulation physiotherapy service), HRQoL, and functional capacity, will be evaluated for group differences using mixed effects ordered logistic regression, with mean time (95 % CI) estimated for descriptive purposes using mixed effects linear regression, with or without log transformation depending on distribution. Hospital costs associated with the interventions will be compared using mixed effects linear regression. Log transformation of highly skewed cost data will be performed.

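### The secondary time outcomes have no defined value after in-hospital death or an unreached milestone, length of stay has two start points, and the Kaplan-Meier graph of PPC can overstate in-hospital incidence

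*Protocol article*

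**What the plan says.** - **Definitions (Secondary trial outcomes).** Hospital length of stay is counted "from the day of admission to the day of discharge" into community living, and time in rehabilitation or at another hospital is included. The ambulation and physiotherapy-discharge outcomes are times to reaching a milestone. Unplanned ICU admission counts whenever it occurs in the acute stay.
- **Follow-up.** Under Standardisation of post-operative procedures, daily sessions end at the physiotherapy discharge score or at hospital discharge. Under Post-operative variables, the lead-in reads "Post-operative data will be collected daily for 14 days or until discharge from hospital, whichever occurs first". The list below it includes total hospital stay, ICU/HDU stay and unplanned ICU admission.
- **Analysis (Statistical methods).** "ICU and total post-operative LOS, time to ambulation for 1 and 10 min" and time to physiotherapy discharge are compared by mixed effects ordered logistic regression. Linear regression supplies mean times for description. All outcomes are declared intention-to-treat. Multiple imputation is the only provision for missing data, as a sensitivity analysis.
- **Time to PPC.** This is analysed by Cox regression: "Graphic representation of this analysis will be performed using the Kaplan-Meier method".

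**The concern.** The article fixes the end point, the follow-up and the model for each time outcome, and the three do not fit together for participants who never reach the end point. These are likely to be the sickest or slowest, and the Background itself links PPC to mortality and longer stay. If the intervention changes how many of them there are, leaving them out or scoring an early exit as an early success distorts the comparison of recovery. The distortion works against the arm with fewer of them.

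The PPC graph raises a related problem. Discharge ends observation and is not independent of PPC risk, so how it enters the Kaplan-Meier estimate matters. Stay is itself an outcome that the intervention is meant to influence.

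**Working it through.** **1. The plan's own figure.** The sample size serves only to set the arm size below. Inputs from Sample size: "0.05 two-sided significance level" and "80 % power to detect a 10 % absolute difference in PPC", with 10 % against 20 %. Pooled-variance formula per arm:

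n = [1.960 × √(2 × 0.15 × 0.85) + 0.842 × √(0.2 × 0.8 + 0.1 × 0.9)]² / 0.10² = (0.990 + 0.421)² / 0.01 ≈ 199

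The total is 398, as stated. 398 × 1.11 = 441.8, against a stated 441. Nothing below changes these figures.

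**2. Who has no value.**

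| Outcome | Dies in hospital | Goes home alive before the milestone |
|---|---|---|
| Hospital length of stay | End point never occurs | Not applicable: live discharge is the end point |
| ICU length of stay | Has a value, misleadingly short if death is in ICU | Not applicable |
| Ambulation >1 min, >10 min | No time if not yet reached | No time |
| Physiotherapy discharge | No time if not yet reached | No time |

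The protocol expects some of this, since reasons are to be recorded when 10 minutes of walking is not achieved. Data management makes outcome fields mandatory, but the article does not say what to enter. Imputing a time for someone who died would invent a recovery.

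**3. How many.** The document gives no rates. *Assumptions:* 2–5 % die and 5–15 % never reach a given milestone in hospital. Then 0.02 × 441 = 9 to 0.05 × 441 = 22 deaths, and 22 to 0.15 × 441 = 66 non-reachers.

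**4. Consequence for the comparison.** Simulation with 199 per arm and 1,500 replicates. *Assumptions:* log-normal milestone time with median 4 days and log-SD 0.6; non-reachers drawn from the slowest 20 %; the Wilcoxon test standing in for unadjusted ordered logistic regression. A real effect is a log shift of −0.15, that is 1 − e^(−0.15) = 14 % shorter.

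| Not reached, control / intervention | Effect on time | Rejection: dropped | Rejection: exit day | Rejection: ranked worst |
|---|---|---|---|---|
| 5 % / 5 % | none | 5.7 % | 6.1 % | 3.3 % |
| 8 % / 3 % | none | 14.3 % | 14.5 % | 4.6 % |
| 15 % / 5 % | none | 38.6 % | 35.1 % | 5.4 % |
| 8 % / 3 % | 14 % shorter | 40.7 % | 40.2 % | 68.9 % |

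With equal rates, the probability that a control participant takes longer is 0.50 under every rule. With unequal rates and no effect, it falls to 0.45–0.48 when non-reachers are dropped or entered at exit day, so the intervention looks slower.

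**5. Kaplan-Meier for PPC.** Simulation of 400,000 stays. *Assumptions:* 20 % PPC risk, onset at 1 day plus an exponential time with mean 2.5 days, log-normal stay with log-SD 0.45, and discharge treated as censoring.

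| Median stay | Stay prolonged past PPC onset | In-hospital PPC | 1 − KM | Excess (points) |
|---|---|---|---|---|
| 8 days | yes | 19.9 % | 23.9 % | 4.0 |
| 6 days | yes | 19.8 % | 31.3 % | 11.5 |
| 8 days | no | 18.1 % | 19.9 % | 1.8 |
| 6 days | no | 16.5 % | 19.9 % | 3.4 |

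If those discharged alive are instead kept event-free in the risk set to day 14, Kaplan-Meier equals the crude proportion.

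**6. Internal mismatches.** Length of stay starts at admission in Secondary trial outcomes and is post-operative in Statistical methods. The 14-day lead-in in Post-operative variables does not fit total stay or unplanned ICU admission as Secondary trial outcomes defines them.

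**The case against.** The strongest reply is that this is a coding rule, which an article may leave to an analysis plan that is not shown. Ordered logistic regression can hold death or non-attainment as a worst category. That is right about the model. A reader might infer that the plan drops or mis-ranks these participants; it says neither, and the fault lies in outcomes and models that do not fit without a rule.

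Other stronger readings also fail:

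- That leaving hospital alive deprives a participant of a length of stay. It does not; it ends it.
- That readiness for discharge is mis-analysed. Statistical methods does not name an analysis for it.
- That length of stay and ICU admission are cut off at day 14. Secondary trial outcomes carries both further, and the 14-day lead-in cannot govern its whole list, which even includes the interval from the pre-operative session to surgery. The ambulation items stand in a separate paragraph without that limit.
- That Kaplan-Meier will report a PPC incidence near 31 %. Absolute rates come from Poisson regression, the curve only illustrates the Cox analysis, and the article does not say that discharge is censored. The largest excess needs stay to be prolonged past every PPC onset.

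Non-attainment may also be limited, because patients unable to walk are excluded and interval walking counts. What remains is the undefined values, the two start points, the ill-fitting lead-in, and a graph whose meaning depends on how discharge is treated.

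**Conclusion.** The point holds for secondary outcomes and one graph. By the article's definitions, in-hospital deaths have no length of stay, and participants who die or leave before a milestone have no time for it. The named models need a value and none is defined, which sits badly with intention-to-treat for all outcomes.

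The size cannot be taken from the document. It is negligible with equal rates up to about 5 %. With assumed rates of 8 % against 3 % up to 15 % against 5 %, false rejection rises to about 14–39 %. With a real 14 % shortening and 8 % against 3 %, power is about 41 % instead of 69 %. These figures rest on non-reachers coming from the slow end of the distribution.

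The excess on the Kaplan-Meier graph, if discharge is censored, is about 2–3 points without prolonged stay and 4–12 points with it. The start-point mismatch is plain on the page, though small in elective surgery. The primary Poisson comparison and the sample size are unaffected. The change should be made, but the trial does not depend on it.

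**What to change.** 1. In the ordered logistic models already planned, rank in-hospital death worst and milestone not reached by discharge next worst. Do not impute times for participants who died.
2. Use one start point for length of stay in both Secondary trial outcomes and Statistical methods. State that length of stay, ICU days and unplanned ICU admission are exempt from the 14-day limit in Post-operative variables.
3. Show time to PPC as cumulative incidence to day 14, with discharge alive and death without PPC as competing events. Alternatively, keep those discharged alive event-free in the risk set to day 14. Describe the Cox result as a cause-specific hazard ratio.

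The cost is wording in the definitions and analysis sections; no extra participants or visits are needed, and discharge dates are already in hospital records. The downside is that milestone effects are reported as an ordinal shift, with mean times descriptive only.

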### Control group

Participants will have a standardised assessment conducted by a physiotherapist consisting of: questioning on current health co-morbidities, mobility and functional status, smoking history, lung auscultation, subjective assessment of cough quality and strength, sputum production and colour, hand grip strength, Rapid Assessment of Physical Activity (RAPA) [57] and Specific Activity Questionnaire (SAQ) [58] to determine current activity and fitness levels, and Short Form 36 (SF-36 V2) [59] to measure HRQoL (see Data Collection section for further details). Participants will then be provided with an education booklet. This colour booklet contains written and pictorial information about abdominal surgery, expected types of pain management, medical lines and drains, post-operative recovery process, and how to prevent post-operative respiratory complications with early ambulation and self-directed DB&C exercises. The booklet includes detailed written instructions to perform DB&C exercises for two sets of 10 deep breaths followed by three coughs every hour during waking hours. Participants will be instructed to bring the booklet to hospital for reference following the operation. The contents of the booklet will not be discussed with participants in the control group and there will be no additional physiotherapy provided pre-operatively.

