## Data collection

### Pre-operative variables

To measure baseline characteristics the following variables will be collected directly from the patient or the medical record: centre of recruitment, age, gender, height (cm), weight (kg), body mass index (kg/cm^2^), planned surgical procedure, category (hepatobiliary/upper gastrointestinal, colorectal, renal and urology, vascular, or other) and reason for the procedure, physical health status according to the American Society of Anaesthesiologists (ASA) and rated by the attending anaesthetist at the PAC (score 1 to 5), chemotherapy during the preceding 6 weeks, presence of a nasogastric tube before operation, respiratory status (auscultation signs and patient report of a daily productive cough), cough strength and presence of sputum (patient is asked to cough forcibly, the physiotherapist makes a subjective scoring of strength, effectiveness, and presence of sputum), sputum class (mucoid, mucopurulent, purulent) and colour using a validated colour chart tool [68] of any observed or patient reported regularly produced bronchial secretions, patient-reported history of a chest infection in the previous 14 days and if antibiotics had been prescribed, smoking history (non-smoker, current smoker, or ex-smoker having ceased more than 8 weeks pre-operatively), smoking pack years (1 pack year = 20 cigarettes per day for 1 year), years since smoking cessation, SpO_2_ (%) on room air, heart rate (beats per minute), co-morbidities as documented in the medical record (history of stroke or any other type of debilitating neurological disease, diabetes, arthritis, osteoporosis, asthma, COPD or other type of chronic respiratory disease, history of an acute myocardial infarct or angina, peripheral vascular disease, upper gastrointestinal disease such as reflux or gastric ulceration, current depressive illness or anxiety/panic disorder, visual or hearing impairment), patient’s self-report if the listed comorbidities significantly limit their walking on a day-to-day basis, Functional Comorbidity Index score [69], HRQoL with the SF-36, patient-reported estimated maximum metabolic equivalent (MET) physical activity using a self-rated physical Specific Activity Questionnaire (SAQ) [58], patient-reported measure of physical activity status using the Rapid Assessment of Physical Activity (RAPA) questionnaire and categorised to sedentary, under active, under active regular light activities, under active regular, and active [57], patient-reported maximum walking time along flat ground at comfortable walking pace, any limiting factor for mobilisation, and maximum grip strength as measured on the dominant hand using a calibrated hand dynamometer (Jamar Plus+; Sammons Preston, Rolyon, Bolingbrook, IL) performed with patients seated with shoulders adducted, elbows flexed to 90°, and forearms in the neutral position. The dynamometer handle position will be set to the second position for all tests [70], and three tests will be performed with verbal encouragement with the best test result recorded.

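### The 6-week SF-36 and SAQ comparisons do not prespecify adjustment for the same instrument's baseline score, and the stated stepwise rule would leave it to the data

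*Protocol article*

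**What the plan says.** **Baseline.** In the protocol article, the control-group assessment includes "Short Form 36 (SF-36 V2) [59] to measure HRQoL" and also the SAQ. The Intervention group section gives that arm the same assessment. The Pre-operative variables section lists "HRQoL with the SF-36, patient-reported estimated maximum metabolic equivalent (MET) physical activity", the latter measured by the SAQ.

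**Follow-up.** Secondary trial outcomes names the SF-36 and SAQ again, at 6 to 8 weeks after surgery.

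**Analysis.** Statistical methods says "HRQoL, and functional capacity, will be evaluated for group differences using mixed effects ordered logistic regression". These two outcomes share one recipe with length of stay and time to ambulation, which have no baseline value. The option of analysing with or without covariates is written out only for the Poisson and Cox models of PPC.

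**Covariates.** The same section has adjusters chosen by backward stepwise regression from a list of candidates, mostly respiratory, surgical and anaesthetic. The list is introduced as examples, so it is not closed. Baseline SF-36 is not on it. One entry refers to physical activity as reported by the patient, which could mean the RAPA, the SAQ or both.

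**Sample size.** The trial has "80 % power to detect a 10 % absolute difference in PPC" at a "0.05 two-sided significance level" and "when the sample size is 398". No power is stated for SF-36 or SAQ.

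**The concern.** When an outcome is measured on the same instrument before and after randomised treatment, its own baseline is usually among its best predictors. Conditioning on it raises power and removes the part of any chance baseline difference that would otherwise carry into the estimate. Here the data are already planned for collection, but nothing secures their use. If baseline SF-36 never enters as a candidate, it is not used. If it does enter, backward selection may drop it.

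The sample was sized for PPC alone, so any extra precision for the patient-reported outcomes has to come from the analysis. The article's Discussion stresses the importance of patient-reported quality of life and hypothesises that it may improve.

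**Working it through.** **1. The plan's own figure.** Inputs from Sample size: PPC 20 % against 10 %, two-sided 0.05, 80 % power. Equal allocation is assumed because that section states no ratio. With pooled variance under the null,

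n per arm = [1.960 × √(2 × 0.15 × 0.85) + 0.842 × √(0.20 × 0.80 + 0.10 × 0.90)]² / 0.10² = 199, so 398 in total.

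This matches the stated 398. It concerns PPC only and serves here just to fix the number analysed. The number with 6-week data may be smaller, but the ratios below do not depend on it.

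**2. Linear model.** The document gives no baseline to 6-week correlation r and no standard deviation. I assume r = 0.3 to 0.7 and work in SD units. The lower end matters because major surgery falls between the two measurements.

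- Variance ratio, adjusted to unadjusted: 1 − r²
- Effective sample size gain: 1/(1 − r²)
- Smallest difference detectable with 80 % power, unadjusted: (1.960 + 0.842) × √(2/199) = 0.281 SD
- The same, adjusted: 0.281 × √(1 − r²)

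| Assumed r | 1 − r² | Fall in standard error | Gain | 398 equivalent to | Detectable difference | Power at 0.281 SD |
|---|---|---|---|---|---|---|
| none (unadjusted) | 1 | – | 1 | 398 | 0.281 SD | 80 % |
| 0.3 | 0.91 | 5 % | 1.10 | 437 | 0.268 SD | 84 % |
| 0.5 | 0.75 | 13 % | 1.33 | 531 | 0.243 SD | 90 % |
| 0.7 | 0.51 | 29 % | 1.96 | 780 | 0.201 SD | 97.5 % |

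**3. The planned model type.** The formula 1 − r² belongs to linear regression, so the gain was checked by simulating ordered logistic regression. The set-up was 398 participants, 1:1, a normal score cut into 10 categories, an effect of 0.281 SD, and centre not modelled. Power used 300 runs per r, and the standard error of the log odds ratio came from a separate set of 120 runs per r.

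| Assumed r | Power, unadjusted to adjusted | Mean SE of log odds ratio, unadjusted to adjusted |
|---|---|---|
| 0.3 | 74 % to 78 % | 0.176 to 0.177 |
| 0.5 | 77 % to 84 % | 0.176 to 0.178 |
| 0.7 | 78 % to 98 % | 0.176 to 0.182 |

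With 300 runs, a power near 77 % has a simulation error of about √(0.77 × 0.23/300) = 2.4 percentage points, so the spread among the unadjusted figures is noise. Power rises with r while the standard error does not fall. Conditioning on a prognostic baseline moves the odds ratio from marginal to conditional, further from 1, and the power comes from that larger estimate.

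**The case against.** The strongest objection is that the article is silent rather than wrong. It never says that the 6-week scores will be analysed unadjusted, its candidate list is open, and a fuller analysis plan that is not shown may name the baseline term. A reader might infer that the protocol has chosen to compare follow-up values only. The text does not support that reading, and I do not make it. What remains is that the article does state a covariate rule, and that rule cannot guarantee adjustment for the outcome's own baseline even if the score becomes a candidate.

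For SAQ, the activity entry may already make the baseline score a candidate, since the Control group section describes RAPA and SAQ together as measures of current activity and fitness. That stands, so the point is strongest for SF-36. Candidacy still does not mean retention.

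Statistical methods also opens by saying that the size and prognostic strength of baseline imbalances will be assessed. This goes part of the way, but a covariate decision made after looking at imbalance is again data-dependent.

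Two further inferences would go too far. One is that omitting baseline widens the interval on the odds ratio; step 3 shows that it does not in the planned model. The other is that every participant will have a baseline score. Collection is planned for all, but enrolment by telephone is allowed and completeness is not documented.

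**Conclusion.** The point holds as a low-cost improvement to secondary analyses. As written, the plan does not secure adjustment of 6-week SF-36 and SAQ for their own baseline, and the one rule it gives leaves the matter to stepwise selection. Randomisation protects the comparison from bias, and the PPC analysis is untouched. The cost is lower power and exposure to chance baseline imbalance.

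The size rests on an assumed correlation. Across r = 0.3 to 0.7, linear-model residual variance falls by 9 to 49 %. In the ordered logistic simulation, power rises by about 4 percentage points at r = 0.3 (within simulation error of the unadjusted spread), 7 at r = 0.5 and 20 at r = 0.7. The gain may therefore be small or substantial, and the document cannot settle which.

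**What to change.** In Statistical methods, state that each 6-week model includes, as a prespecified covariate exempt from stepwise selection, the baseline value of the same SF-36 domain or summary score, or of the SAQ, together with centre. Apply this to the ordered logistic models and to any linear model used to describe these scores.

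Report the odds ratio as conditional on baseline, because adjustment changes what it estimates. Include baseline SF-36 and SAQ in the multiple-imputation model, whose contents the article does not list.

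The cost is a few sentences of analysis wording, best fixed before unblinded data are seen. No new data collection or change in sample size is needed.
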